#### II.Data preprocessing

All video files saved from the ultrasound (US) devices and the frames separated by the OB-GYN/Cardio (OBC) department into folders corresponding to the key planes are collected into the cloud. The Data Science / IT department (DSIT) will process the frames for obeying the anonymization regulations. This implies two essential aspects. One is obviously to erase the information that refers to the patients from the frame samples and the video files, as file and folder names. However, before deleting such information, unique strings will be assigned to each patient, such that, when separating the samples into sets for training, validating, and testing the model, all images that belong to the same patient will be placed in only one of the three sets. In the case that some samples from a patient would be placed in the training set and other samples from the same patient would be put in the validation (or test) set, the machine learning model would be biased since these samples would be more similar compared to those coming from different patients. Hence, before the anonymization takes place, unique codes will be generated for each patient in turn, and the code will appear on the names of the files.

Subsequently, the samples of the patients will be split into training, validation, and test sets, keeping the proportions of 60–20%-20%. These approximate proportions need to be kept for each class in turn. As mentioned above, images belonging to the same patient will be placed in the same set, be it training, validation or test. In addition, even if the samples come from a different video file but from the same patient, e.g., if the patient went to a consultation at another date, the samples will be placed in the same folder to avoid biasing the model.

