#### IV. Experiments

All the recent DL entries will be tailored and tested on the current scenario of key view identification. Their prediction results will be analyzed compared to the ground truth marked by the OBC. The metrics concern accuracy, precision, recall, and F1-score. A hierarchy will be built based on statistical testing, and the best algorithm will represent the AI module for this scenario. Different architectures can be tried. Some have a relatively small number of layers, and they are faster as concerns running time. Others are very deep, meaning that they have a high number of layers hence they take longer to train but are potentially more accurate. It is essential to be fast in the testing stage for the final trained model used in practice, as the training model would not be later re-initiated. Although the more complex models still run slower in the testing phase than those with fewer layers, the differences are minimal. However, the current task needs to be thoroughly tested since it might be the case that shallow models also lead to accurate results and, if this is the case, they will be preferred. The accuracy-speed equilibrium will be considered when ranking the approaches since the system will finally perform on a video.

Once a new video is available in practice, the model chosen for the task will highlight each key feature and the probability/certainty. Additionally, the final application will present a graphical and numerical report showing the number of frames with key planes identified and the indication of the certitude it has for them. Finally, the OBC physicians will validate all the intermediary findings at frame level and the meaningfulness of the video labeling.

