#### Secondary outcomes

The increase in the rate of satisfactory evaluations of the heart key-planes in first trimester scans by inexperienced and newly trained sonographers.The optimization of the ultrasound clinical workflow using AI as an assistant for the FE practice through a time- efficient video labeling, i.e., a video frame processed in less than 20 milliseconds. Several options could be tried to achieve this, and the optimal decision will perhaps include all of them. We intend to vary the preprocessing options since some might be time-consuming. Another option refers to resizing the input images to a smaller dimension as long as the accuracy does not significantly decrease since they are faster to process when the size of the input data is reduced. Changing the deep learning model architecture to one with fewer layers would also reduce the amount of time for the processing of video frames.A reduced rate of diagnosis discrepancies between evaluators with different experience.

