### Statistical methods

There will be several deep learning architectures trained on the obtained data set. In order to select the most prolific one and be assured that its results are not based on chance, the performance of the different models tried in terms of the considered metrics will be assessed under random sub-sampling cross-validation with multiple repetitions and the significance in the difference of the results will be checked via a Wilcoxon signed-rank test.

The performance of the computational models on videos taken by inexperienced sonographers will be statistically assessed compared to the results on scans where an expert made the examination. In order to achieve this, two sets of video scans will be completed, one containing video files made by experienced sonographers and the other made by inexperienced ones. The frames that the computational model labels will be extracted from the scans, and the experienced physicians will validate their predictions for both types of data. A t-test and a Mann-Whitney test for independent test samples will be used for verifying the differences in the results on the two sets.

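### The Wilcoxon signed-rank test over repeated random sub-samples treats overlapping repetitions as independent, so its error rate exceeds the nominal level and depends on how many repetitions are run

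*Protocol article*

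**What the plan says.** Statistical methods, first paragraph: "There will be several deep learning architectures trained on the obtained data set". The comparison is described as "random sub-sampling cross-validation with multiple repetitions and the significance in the difference of the results will be checked via a Wilcoxon"; the form named is the signed-rank test. The purpose is stated as well: "In order to select the most prolific one and be assured that its results are not based on chance".

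Section IV (Experiments) uses the result: "A hierarchy will be built based on statistical testing, and the best algorithm will represent the AI module for this scenario".

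Section II (Data preprocessing) splits the samples into training, validation and test sets, "keeping the proportions of 60–20%-20" per cent, with all images of one patient kept in one set. Section V (Sample size calculation) aims for at least 6000 images from about 300 videos.

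The article gives no number of repetitions beyond saying there will be several. It states no significance level and names no correction for overlap between repetitions.

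**The concern.** The signed-rank test needs independent pairs. The only pairs the text supplies are the repetitions: in each one, both models are trained and scored on the same random split, and the difference is recorded. All splits come from one pool of patients, so any two repetitions share many training patients and some test patients. If one model happens to suit this pool better, most repetitions will show it, and the test counts each showing as fresh evidence.

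More repetitions narrow the average towards a value fixed by the patients in hand. They say nothing more about new patients. The test nevertheless becomes more confident with each one. Keeping each patient in a single set prevents leakage within a split, but it does not make separate splits independent.

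At stake is the ranking of the architectures. Two equally good models can be reported as significantly different, and whether they are depends partly on how many repetitions were run. A shallower, faster model could be ranked below a deeper one that is no better.

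**Working it through.** The plan gives no error rate, power or repetition count for this comparison, so there is no figure of its own to reproduce.

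**Inputs**
- Split 60/20/20 by patient: section II. Applying it to each random repetition is an assumption.
- 300 videos and 6000 images: section V, giving 6000/300 = 20 images per video. One video per patient is an assumption.
- Two-sided alpha 0.05: assumption.
- Number of repetitions J: not stated; 6 to 100 examined.
- Correlation rho between the differences of two repetitions: not stated. The usual approximation for these splits is test/(test + train) = 0.20/(0.20 + 0.60) = 0.25. Retraining noise could lower it, so 0.10 to 0.25 is used.

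**Formula.** Let each difference have variance s² and correlation rho with the others.
- True variance of the mean over J repetitions: s²[1 + (J−1)rho]/J. This does not fall below rho·s², however large J is.
- Variance implied by treating repetitions as independent: s²(1−rho)/J on average.
- Ratio: [1 + (J−1)rho]/(1−rho) = 1 + J·rho/(1−rho).

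At rho = 0.25 the ratio is 1 + J/3. The standard error is then too small by √4.33 = 2.1 at J = 10, √11 = 3.3 at J = 30 and √34.3 = 5.9 at J = 100. The normal approximation P(|Z| > 1.96/factor) gives error rates of about 0.35, 0.55 and 0.74.

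**Simulation of the signed-rank test.** Share of equal models declared different at nominal 0.05:

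| Setting | J=6 | 10 | 20 | 30 | 50 | 100 |
|---|---|---|---|---|---|---|
| rho 0 (independent) | 0.030 | 0.049 | 0.050 | 0.050 | 0.050 | 0.050 |
| rho 0.10 | 0.064 | 0.147 | 0.248 | 0.330 | 0.426 | 0.559 |
| rho 0.20 | 0.106 | 0.247 | 0.391 | 0.477 | 0.579 | 0.688 |
| rho 0.25 | 0.136 | 0.295 | 0.444 | 0.538 | 0.631 | 0.728 |
| 300 patients, 20% test sets redrawn | 0.104 | 0.240 | 0.398 | 0.510 | 0.590 | 0.702 |
| Same, with added retraining noise | 0.068 | 0.156 | 0.258 | 0.331 | 0.433 | 0.570 |
| Two classifiers actually retrained | 0.105 | 0.220 | 0.352 | 0.420 | 0.523 | not run |

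The rho rows use 20,000 runs and the two redraw rows 2,000. The last row uses 600 data sets of 300 patients × 20 frames, five classes and two exchangeable linear classifiers; its estimated rho was 0.17. The first row shows that dependence is the cause: with independent repetitions the test holds its level.

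**Small J.** The smallest exact two-sided p-value with 5 pairs is 2/2⁵ = 2/32 = 0.0625, so with 5 or fewer repetitions nothing can be significant at 0.05.

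**Check of the remedy.** Rejection rates of a t-test with variance factor 1/J + n_test/n_train = 1/J + 20/60 = 1/J + 1/3:

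| rho | J=6 | 10 | 20 | 30 | 50 | 100 |
|---|---|---|---|---|---|---|
| 0.25 | 0.051 | 0.051 | 0.049 | 0.050 | 0.051 | 0.049 |
| 0.20 | 0.037 | 0.035 | 0.028 | 0.029 | 0.027 | 0.025 |
| 0.10 | 0.018 | 0.009 | 0.005 | 0.003 | 0.002 | 0.001 |

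**The case against.** The best case against the point concerns its size and reach.

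**Size.** A reader might infer one large inflation factor for the plan. The article supports none, because J and alpha are unstated. At J = 6 the error is only 0.064/0.05 = 1.3 to 0.136/0.05 = 2.7 times nominal. With actual retraining at J = 10 it is 0.22/0.05 = 4.4 times. This stands, so the size must be given conditional on J.

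**Selection.** A reader might infer that the choice of module rests wholly on this p-value. It does not. Section III saves the model most accurate on the validation set. Section IV weighs accuracy against speed, prefers shallow models if they prove accurate, and calls testing-phase speed differences minimal. A false positive between two equally good models still selects a good model. The harm is an unsupported claim of superiority or a somewhat slower module. This also stands.

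**Image size.** Secondary outcomes allows "resizing the input images to a smaller dimension as long as the accuracy does not significantly decrease", and a reader might infer that the same test decides this. The sentence names no test, does not refer to Statistical methods, and may use the adverb loosely. The link is not supported.

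**Multiplicity.** A reader might add a count of pairwise tests over architectures, preprocessing scenarios and metrics. The article does not say how many architectures there will be or that every pair is tested, and it compares the preprocessing scenarios on accuracy without naming this test. Such detail commonly sits in the fuller plan.

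**Meaning of equal.** If the question were only which model does better on this fixed pool, the test would mislead less. But the module is meant for new videos, so excluding chance has to mean chance in the patients sampled.

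None of this removes the core. The resampling scheme, the test and its purpose are all stated, and the combination cannot serve that purpose. That is a wrong method, not an omitted detail.

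**Conclusion.** Wrong as written, and it should be fixed before models are compared. The signed-rank test over repetitions does not control the chance of declaring equal models different, and its p-value depends on a repetition count left to the analyst. For rho from 0.10 to 0.25 the error is about 6–14% at J = 6, 15–30% at J = 10, 33–54% at J = 30 and 56–73% at J = 100; the test has no power to reach 0.05 at J ≤ 5. These figures assume two-sided alpha 0.05 and patient-level 60/20/20 splits in each repetition, with equality meaning equal expected performance on new patients.

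The consequence is limited to the part of the model hierarchy that rests on statistical testing. The comparison of experienced with inexperienced sonographers uses other tests and is not affected by this point.

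**What to change.** In Statistical methods, state the number of repetitions J in advance and replace the Wilcoxon signed-rank test over repetitions with one of the following:

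- **Corrected resampled t-test**: mean difference divided by the square root of (1/J + n_test/n_train) times the sample variance of the differences, on J − 1 degrees of freedom. For 60/20/20 splits the factor is 1/J + 1/3.
- **Paired patient-level bootstrap** of the metric difference within the development data, resampling patients and not frames. If the models are not retrained in each resample, say that the interval is conditional on the trained models.

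The cost is a change of wording and a few lines of analysis code, with no new patients or scans. The downside is that fewer models will be declared different. The corrected t-test is also conservative when the correlation is below 0.25, as the remedy table shows. Where models cannot be separated, validation accuracy and speed, which section IV already weighs, can decide without a claim of significance.

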##### Data set organization

Figure 2 presents a bird’s-eye view of the entire protocol. In order to create a deep learning model that would accurately identify the key-planes in a US video, a high number of samples for each of the four categories represented in Fig. 1 is necessary. Accordingly, all US videos that will serve for the training of the computational model will be split into separated frames. The physicians will select the appropriate images from these frames showing the cardiac key planes and distribute them to dedicated folders. These will be placed on a shared folder in cloud storage, where both physicians and computer scientists working on the task will have secured access. This way, multiple doctors can contribute with data, and, at the same time, the machine learning experts can access the continuously growing data set. Also, all the fetal echocardiograms from 2018 to the present will be reviewed to include them in the data set that will train the IS.

The video files will also be uploaded, besides the images separated in different folders based on the key planes classification. The uploaded videos will serve for automatic extraction of the frames that do not contain satisfactory key planes views.

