#### III. Frame Classification

As previously stated and illustrated in Fig. 2, the deep learning model needs another class to be learned, apart from the ones illustrated in Fig. 1. This class should not contain any key plane; hence we labeled it *other*, meaning it is unimportant (not informative). It will be appointed to make the machine recognize the key features from the sweeping, where the majority represents noise or transition between the views. They do not belong to any of the key planes, and the model should appropriately identify them as not informative. Contrarily, if the model were trained without the *other* class, for each frame that does not contain a particular plane, the algorithm would feel forced to label it with one of the classes of interest, even if that image does not represent anything of value for the detection.

Accordingly, the saved US video files will allow the automatic extraction of the frames that do not confidently present any of the key planes, i.e., the *other* samples. The images extracted from the video frames by the OB-GYN experts will be used for comparison with the frames from the video files, and, when the similarity is below a certain threshold, the frames will be considered distinct enough from the images of the key planes and will be saved to the *other* folder. The number of such non-important images can be very high, but it will be controlled by establishing an adequate number of samples, i.e., around 30% more samples than in the class with the most images. The higher the quantity of the images in the *other* class, the better the model will learn. If not enough samples are assigned to this class, images that do not contain key planes may be labeled as being from such classes. Hence, it is crucial to have a proper value for the number of items in class *other*, and this value will be empirically determined. After these transition samples are extracted, the human experts will again check the samples to ensure that key planes would not be included by mistake. DSIT will try different state-of-the-art DL pre-trained algorithms on the data set with the plane views. The training will take place only on images, not on video files at this stage. After training, the model that proved to be the most accurate on the validation set will be saved, and it will be included in an application that will be able to deal with video files.

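### In the experienced-versus-inexperienced video comparison, physicians check the model's own output, so a loss of recall may be largely hidden

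*Protocol article*

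**What the plan says.** The section Statistical methods plans two sets of videos, one made by experienced and one by inexperienced sonographers. For both sets, "The frames that the computational model labels will be extracted from the scans, and the experienced physicians will validate their predictions". The two sets are then compared: "A t-test and a Mann-Whitney test for independent test samples will be used for verifying the differences in the results on the two sets". No metric is named for this step.

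The section IV. Experiments describes a similar check in general terms: "Finally, the OBC physicians will validate all the intermediary findings at frame level and the meaningfulness of the video labeling".

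The image-level work follows a different order. Under Data set organization, before any model is trained, "The physicians will select the appropriate images from these frames showing the cardiac key planes and distribute them to dedicated folders". Under IV. Experiments, "Their prediction results will be analyzed compared to the ground truth marked by the OBC", and "The metrics concern accuracy, precision, recall, and F1-score".

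The section III. Frame Classification adds a class *other* for noise and transition frames, which make up most of a sweep: "They do not belong to any of the key planes, and the model should appropriately identify them as not informative".

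**The concern.** In the video comparison the model runs first, its output decides which frames are extracted, and the physician then validates that output. Two weaknesses follow.

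- **Selection.** If the extracted frames are those labelled as key planes, a true key-plane frame that the model called *other* is not shown to a physician. False negatives are then unknown. What can be estimated is the share of flagged frames that are right, which is precision.
- **Dependence.** Even if every frame is extracted, the physician is asked to confirm or reject an existing answer. That reference is not independent of the prediction, and borderline frames may tend to be accepted.

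This comparison is the only analysis described that tests the model on inexperienced operators' scans. Those operators are the intended users in the primary outcome and in the first secondary outcome. If the model misses more key planes on their scans, this is where it should show.

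**Working it through.** The protocol gives no figure for this step, so there is none to reproduce. The check has two parts.

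**1. What the wording allows**

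| Reading of the frames the model labels | Support | Consequence |
|---|---|---|
| Key-plane labels only | Frames are extracted from the scans, which implies selection. The application's report counts frames with key planes (IV. Experiments). | Misses not reviewed; recall and F1 not estimable |
| All labels, including *other* | *Other* is a trained class, so every frame can receive a label. The caption of Fig. 2 has the model classifying frames of new videos. | Misses countable; reference still depends on the prediction |

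The first reading is the more natural one, but the text does not settle the matter.

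**2. Size under the first reading**

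All inputs here are assumptions: 1000 frames; key plane versus *other* treated as two classes; specificity 0.97; key-plane share 10%, 20% or 40%; recall falling from 0.95 to 0.60.

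- Agreement on reviewed frames = TP / (TP + FP), which is precision.
- F1 = 2TP / (2TP + FP + FN).

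At a 20% share there are 200 key-plane frames and 800 others, so FP = 0.03 × 800 = 24.

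- Recall 0.95: TP = 190, FN = 10. Agreement = 190/214 = 0.888. F1 = 380/414 = 0.918.
- Recall 0.60: TP = 120, FN = 80. Agreement = 120/144 = 0.833. F1 = 240/344 = 0.698.

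Missed key-plane frames rise from 10 to 80. F1 falls by 0.220 and the reviewed-only result by 0.055.

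| Key-plane share | FP | Agreement, recall 0.95 → 0.60 | F1, recall 0.95 → 0.60 |
|---|---|---|---|
| 10% | 27 | 95/122 = 0.779 → 60/87 = 0.690 | 190/222 = 0.856 → 120/187 = 0.642 |
| 20% | 24 | 0.888 → 0.833 | 0.918 → 0.698 |
| 40% | 18 | 380/398 = 0.955 → 240/258 = 0.930 | 760/798 = 0.952 → 480/658 = 0.729 |

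**Effect of dependence on the prediction.** Suppose also that a physician who sees the label accepts half of the false positives. At a 20% share, agreement becomes (190 + 12)/214 = 0.944 and (120 + 12)/144 = 0.917. The visible fall shrinks to 0.027.

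**The case against.** The case on the other side has several parts, and much of it limits the point.

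- **Missed key planes are counted elsewhere.** A reader might infer that the study never measures recall. It does: the image-level test set has physician-marked ground truth, and recall and F1 are named there. That stands, so the point covers the video comparison alone. The image set is no substitute, however. The protocol has enrolled women scanned by sonographers with at least three years of fetal cardiac experience (Interventions). Its *other* frames are also chosen for low similarity to key-plane images, which leaves out borderline frames.
- **No metric is promised for the videos.** The four metrics are listed with the image-level experiments, while the video comparison speaks only of results. That stands: this is not a contradiction between two stated commitments. It is a procedure that may prevent the more informative metrics from being computed.
- **All frames may be reviewed.** The wording permits this, and misses would then be countable. The selection problem is therefore conditional.
- **Masking is not mentioned.** A reader might infer that physicians see the prediction and know the operator group. The article states neither, and a condensed article may leave masking to the full protocol. What the text does fix is that physicians validate the model's predictions, where elsewhere they mark ground truth first.
- **A fall in recall is not invisible.** A reader might infer that the comparison would show no change at all. That would need precision to stay constant. At fixed specificity it falls, as the working shows. The application also reports how many key-plane frames it found, so a large drop in yield would appear. That count cannot separate model misses from sweeps in which the plane was never captured.

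**Conclusion.** The point holds for the experienced-versus-inexperienced video comparison, in a conditional form.

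- **Key-plane frames only (the more natural reading):** recall and F1 cannot be estimated in this comparison, and a loss of recall on inexperienced scans would be largely hidden. Across the assumed shares of 10% to 40%, a fall in recall from 0.95 to 0.60 costs 0.21 to 0.22 in F1 but moves the reviewed-only result by only about 0.03 to 0.09. These sizes rest on an assumed specificity of 0.97 that is the same in both groups. They are illustrations, not forecasts for this model.
- **All frames:** misses can be counted. What remains is that the reference is not independent of the prediction, and the protocol gives no basis for sizing that effect.

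The documents do not support extending this to the validation as a whole, or stating as fact that the physicians are unmasked. It is an inexpensive improvement to one analysis and worth making before the videos are read.

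**What to change.** In Statistical methods, replace the validation of predictions with labelling that does not depend on them:

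1. The same experienced physicians label the frames of both video sets, with the model's output and the operator group masked.
2. If labelling every frame is too much, they label all model-positive frames mixed with a random sample of *other* frames from each video, with model labels hidden. Each sampled *other* frame is weighted by the inverse of its sampling fraction.
3. Precision, recall and F1 are computed per video against those labels and then compared between the two sets. Videos in which the physicians find no key-plane frame have no defined recall and are reported separately. This also separates planes that were never captured from planes that the model missed.

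The cost is a re-ordering of an existing task and some extra frames for the same physicians. No new scans or readers are needed. Each sweep lasts 5 seconds, but no frame rate is given, so the number of extra frames cannot be worked out from the document.

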**Methods:**

The cross-sectional study will be divided into a training part of the machine learning approaches and the testing phase on previously unseen frames and eventually on actual video scans.

Pregnant women in their 12–13 + 6 weeks of gestation admitted for routine first-trimester anomaly scan will be consecutively included in a two-year study, depending on the availability of the experienced sonographers in early fetal cardiac imaging involved in this research.

The Data Science / IT department (DSIT) will process the key planes identified by the sonographers in the two- dimensional heart cine loop sweeps**:** four-chamber view, left and right ventricular outflow tracts, three vessels, and trachea view. The frames will be grouped into the classes representing the plane views, and then different state-of-the- art deep-learning (DL) pre-trained algorithms will be tested on the data set. The sonographers will validate all the intermediary findings at the frame level and the meaningfulness of the video labeling.

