#### Interventions

All pregnant women that meet the inclusion criteria will be examined by trained sonographers with at least three years of experience with fetal cardiac imaging.

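### The verdicts that decide the comparison of experienced and inexperienced operators' videos come from physicians whom the protocol neither masks to operator or set nor keeps from judging their own scans

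*Protocol article*

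**What the plan says.** The Statistical methods section forms two sets of video scans, "one containing video files made by experienced sonographers and the other made by inexperienced ones". The frames that the model labels are extracted, and "the experienced physicians will validate their predictions for both types of data". The sets are then compared: "A t-test and a Mann-Whitney test for independent test samples will be used for verifying the differences in the results on the two sets".

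On who validates, the article gives two descriptions. The Abstract (Methods) says: "The sonographers will validate all the intermediary findings at the frame level and the meaningfulness of the video labeling". The Experiments section says instead that "the OBC physicians will validate all the intermediary findings at frame level and the meaningfulness of the video labeling". On who scans, the Interventions section says that eligible women "will be examined by trained sonographers with at least three years of experience with fetal cardiac imaging".

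The nearest safeguard is in the Data preprocessing section, where the data science group is to "erase the information that refers to the patients from the frame samples and the video files" and to put a code for each patient in the file names. The operator, the unit and membership of a set are not mentioned there. No section mentions masking of the validating physicians, mixing of the two sets for review, or a rule against reviewing one's own scans.

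**The concern.** The comparison has a human verdict as its outcome, and its two groups are defined by who held the probe. An error of judgement common to both sets would largely cancel in the difference. An error that depends on the set does not cancel: it goes straight into the contrast that the t-test and the Mann-Whitney test examine.

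Two routes are open. First, a physician who knows the set may treat doubtful labels differently in the two sets. Secondly, the judges are experienced by definition, so a judge who also scanned can meet their own work in the experienced set only.

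This is the only planned analysis that sets experienced against inexperienced operators, and it lies closest to the secondary outcomes about newly trained sonographers. If judgement differs by set, a reported gap, or a reported absence of one, partly describes the judges and not the model.

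**Working it through.** The protocol states no significance level, power, effect size or set size for this comparison, so there is no figure to reproduce. The check is a reading of the sections side by side, then an illustration on stated assumptions.

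**Reading the sections together**

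1. *Outcome.* Statistical methods: physicians decide whether the model's labels are right. The key-plane descriptions under Ultrasound examination (for example equal flows, typical direction, similar diameter) leave some room for judgement.
2. *Judges.* Statistical methods: experienced physicians. Abstract: the sonographers. Experiments: the OBC physicians, whose department also marks the ground truth.
3. *Operators.* Interventions: sonographers with at least three years of experience.
4. *Separation of 2 and 3.* None is stated. Overlap is possible, and the Abstract makes it plausible.
5. *Concealment.* Data preprocessing removes patient information and assigns codes per patient, which does not hide the operator or the set. Two of the three image-preparation scenarios crop away everything outside the image ovals, but they are described as input to the model and not as what the physicians see.

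Followed as written, nothing prevents set-dependent judgement.

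**Illustration (assumptions, not in the documents)**

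Let *p* be the true proportion of correct labels, equal in both sets. Let *f* be the share of wrong labels that is accepted in one set only. Let *n* be the number of frames per set, treated as independent, with a two-sided 5% test of two proportions.

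- False gap = (1 − p) × f.
- Chance of significance in the direction of the distortion = Φ[(gap − 1.96 × SE0) / SE1]. SE0 uses the pooled proportion and SE1 the two separate proportions. With no distortion this chance is 2.5% (5% over both directions).

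Worked case with p = 0.90, f = 0.20, n = 1000:

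- Gap = 0.10 × 0.20 = 0.02, so the sets show 0.92 and 0.90.
- SE0 = √(2 × 0.91 × 0.09 / 1000) = 0.01280.
- SE1 = √((0.92 × 0.08 + 0.90 × 0.10) / 1000) = 0.01279.
- (0.02 − 0.02508) / 0.01279 = −0.397, and Φ = about 0.345.

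| p | f | False gap (points) | n = 500 | n = 1000 |
|---|---|---|---|---|
| 0.80 | 20% | 4 | 37.7% | 64.4% |
| 0.80 | 30% | 6 | 71.5% | 94.7% |
| 0.90 | 10% | 1 | 7.8% | 11.6% |
| 0.90 | 20% | 2 | 19.6% | 34.5% |
| 0.90 | 30% | 3 | 39.8% | 67.2% |
| 0.95 | 10% | 0.5 | 5.6% | 7.6% |

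The reverse direction is just as open. If true correctness were 0.92 in the experienced set and 0.90 in the inexperienced set, and 20% of wrong labels were accepted in the inexperienced set only, the latter would show 0.90 + 0.10 × 0.20 = 0.92. A true gap of 2 points would vanish.

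If judgement does not depend on the set, f = 0 and there is no distortion. Frames from one video are unlikely to be independent, so the percentages only illustrate; the gaps do not rest on that assumption.

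**The case against.** The strongest reply is that the article is silent and does not say that readers are unmasked. Allocation of readers, file coding and order of presentation are details that a condensed article may leave to a fuller protocol. This stands as far as it goes, and it limits the claim to what this document provides for. It does not dispose of the point. The article does say who judges, what is judged, how the sets are formed and what is removed from the files, and that procedure leaves operator and set unconcealed.

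A reader might go further and infer four things that the documents do not support:

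- *The physicians know which set a frame comes from.* The article does not say how frames are presented; they can know, which is not the same as knowing.
- *They review their own scans.* Statistical methods uses different words for those who scan and those who validate, and two units take part. The Abstract makes overlap plausible, not certain.
- *They grade the operator's image.* The verdict concerns the model's label. Whether a heart evaluation is satisfactory belongs to a separate secondary outcome. Judging software gives less motive for partiality than judging a trainee, though some subjectivity remains.
- *The bias favours experienced operators.* Leniency towards colleagues would widen the gap, but a wish to see the tool work for novices would narrow or hide it.

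It is also fair to say that physicians who see the model's label may be drawn towards it. If doubtful frames are more common in one set, this too could differ between sets. Masking to the set does not address it.

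**Conclusion.** The point holds in limited form. The comparison of the two video sets rests on physicians' verdicts, and the protocol provides neither for masking to operator or set nor for keeping physicians from judging scans they made. Set-dependent judgement is therefore possible, with self-review possible in the experienced set only.

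Neither the direction nor the size of any bias can be derived from the documents. On the assumed values in the table, the false gap runs from 0.5 to 6 points; it could be zero or have the opposite sign. Its consequence for the tests depends on set sizes that the article does not give.

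The reach is also limited. The sets are not randomised groups, the comparison is not the primary outcome, and the choice of the model on the validation set is unaffected. The change is still worth making beforehand, because masking cannot be added once the verdicts have been given.

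**What to change.** Add to Statistical methods:

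1. Before validation, the data science group pools the extracted labelled frames of both sets, and the clips too if the physicians are shown them.
2. It removes operator, unit and set identifiers and on-screen overlays, assigns random codes, and presents everything in one random order.
3. No physician validates frames from a scan that they acquired.
4. Set membership is re-attached only after all verdicts are locked.

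The Abstract and the Experiments section should also name the same validators.

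The cost is small. The data science group already anonymises and codes the files, so this adds a recoding and shuffling step and an allocation rule among the existing physicians, with slight scheduling effort and no extra readers or patients. Image quality may still partly reveal the set, so the bias is reduced and not removed. If a fuller protocol already provides for this, one sentence in the article settles the point.
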